### Administrative structure, data coordinating centre, study centre and recruitment

The SMELL trial is designed as a monocentric study performed at the Medical University of Innsbruck (MUI, Austria). The Medical University will also act as sponsor for this trial. Due to the design of the study, no data monitoring committee will be needed. Members of the study team will be trained and are intended to assess the outcomes using validated questionnaires and routine testing batteries. Study data will be recorded using CRFs on paper during each study visit. The investigator will record the participation in a special identification list of patients. This list gives the possibility for later identification of the patient and is expected to be stored at the trial centre. The CRF will not contain personal data that makes identification possible, except for the randomisation number. No special processes to promote data quality (eg, double data entry) will be performed. The study team will also be responsible for the administrative and regulatory function and will manage the final study data. They will adhere to the laws as laid down in the European Regulation 2016/679 and the national data protection law, storing data for at least 15 years. The study team will be supported by the Clinical Trial Centre of the MUI, which is scheduled to execute monitoring of the study progress and data collection at regular intervals. Only the study authors will have access to the final trial dataset.

Patients will be seen in the outpatient department. Interested individuals will be informed by a study team member, explaining the purpose of the study, study design, goals and inclusion/exclusion criteria. An institutional review board/independent ethics committee-approved informed consent form will be handed to individuals considering participation. An amendment regarding patient recruitment was approved by the ethical board, allowing the study team to publish a call for participants in the local newspaper, stating the aim and short description of the study.

### Statistical rationale and outcomes

The primary endpoint of this study refers to the change in total olfactory score between baseline visit and final visit (84 days+14). Statistical analysis is planned to be performed after study completion. No interim analysis of OT efficacy will be performed. Secondary endpoints will be the changes on the multiple questionnaires and scales between baseline and final visit, with gender-related differences as an exploratory endpoint. The questionnaires will include the SF-36 questionnaire (36-item Short Form Survey) and the Hospital Anxiety and Depression Scale (HADS), which is a reliable instrument for detecting states of anxiety and depression in the setting of the hospital outpatient clinic.^30^,^32^ We will also include a German questionnaire focussing on personal well-being (‘Befindlichkeitsskala’), which was shown to be sensitive for change over a short time, and a 10-point visual analogue scale of olfactory function.^33^ Symptom severity will be assessed using Clinical and Personal Global Impression of Severity at each visit. The patient global impression of improvement/clinical global impression of improvement (PGI-I/CGI-I) is intended to be only performed at the final visit after 12 weeks and the follow-up visit after another 12 weeks, if applicable. A descriptive analysis (χ^2^ test for categorical variables, Mann-Whitney U test or unpaired t-test for continuous variables depending on the scale type of the variables) of demographic and clinical data at baseline will be performed. Secondary efficacy criteria will be measured as the change in the other clinical scales and questionnaires between baseline and week 12, except for the PGI-I and CGI-I measures, which will be singularly evaluated at week 12. These measurements are particularly useful as they have been used in clinical studies recruiting patients with different disorders.^34^,^37^ For the analysis of the primary endpoint, we intend to fit a repeated-measures mixed model olfactory function (Sniffin’ Sticks test score) as the dependent variable and a factorial interaction, with between group assignment (training, control) and time (before and after OT) as independent variables. Changes in the total olfactory score (combination of the identification and discrimination subscale of the Sniffin’ Sticks testing battery) and the different scales and questionnaires used in this trial will be given as mean with 95% CI. The same model is planned to be used for the analysis of change of secondary outcome measures (Mood Inventory (Befindlichkeitsskala, Bf-S), Hospital Anxiety and Depression Scale (HADS), Short-Form-36 Health Survey Questionnaire (SF-36)). Comparison will be performed with the χ^2^ test. The PGI-I and CGI-I, which will be singularly evaluated at week 12, will be compared by the non-parametric Mann–Whitney U test. For PGI-I and CGI-I analyses, distributions of dichotomised ratings (amelioration, aggravation) in both groups at the 12-week termination visit will also be compared by the χ^2^ test. For all analyses, statistical significance will be set at the two-sided 5% level.

Missing, unused or spurious primary efficacy data will lead to exclusion of the respective study participant for statistical analysis (eg, drop-out or non-compliance to treatment). Other missing, unused or spurious data will lead to the exclusion of the respective variable for further statistical analysis. Due to the design of the study with assessment of all efficacy variables at only two time points, the primary analysis is intended to be a per-protocol analysis. Therefore, an interpolation of data will not be performed in case of drop-out.

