### Randomisation and unblinding

Randomisation within this single blinded study will take place after obtaining written informed consent, establishing OD and completing the baseline visit. Participants will be randomly assigned to one of the two cohorts in a 1:1 ratio (training cohort vs natural history). We plan to perform randomisation using a computer-generated randomisation schedule provided by the Department of Medical Statistics of the Medical University of Innsbruck (MUI, Austria). The sequence of patient enrolment will correspond directly to their assigned randomisation number. The assignment will not be based on any stratification factors, and no blocking will be applied. The olfactory testing will be performed by one rater, who will be blinded to the group assignment up to the last follow-up.

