Primary outcome	Difference in change of total olfactory score between baseline visit and final visit (84+14 days) between both cohorts
Secondary outcome	Change in subjective olfactory score (VAS) between baseline visit and final visit (84+14 days)Patient/clinical global impression of improvement (PGI-I and CGI-I) at final visit (day 84+14 days)Changes in mood and personal well-being (HADS-A, HADS-D and BF-SR) between baseline visit and final visit (84+14 days)Changes in daily function (SF-36) between baseline visit and final visit (84+14 days)
Exploratory outcome	Gender-related differences on OD and OT
Ethics revision chronology	Name: Ethics Commission of the Medical University of InnsbruckContact: [contact] October 2020: approval of original protocol15 November 2021: Amendment 1: addition of routine otolaryngological examination to exclude non-COVID-19-related nasopharyngeal pathologies19 April 2022: Amendment 2: elongation of study duration till 202518 April 2023: Amendment 3: serum antibodies towards nucleocapsid were added for future participants without PCR results (V.2.3–16 March 2023, current version)12 December 2023: Amendment 4: amendment to publish a call for new participants
IPD sharing statement	Data supporting the results will be archived in an appropriate public repository

BF-SR, Befindlichkeitsskala; FWF, Österreichischer Wissenschaftsfonds; HADS-A, anxiety subscale of the HADS-questionnaire; HADS-D, depression subscale of the HADS-questionnaire; OD, olfactory dysfunction; OT, olfactory training; SF-36, 36-item Short Form Survey; VAS, visual analogue scale.

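### The primary group-by-time model is in effect a change-score test; adjusting for the baseline total score would be at least as precise and remove a regression-to-the-mean shift

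*Protocol article*

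**What the plan says.** The Protocol article, Statistical rationale and outcomes, fixes the primary model: a mixed model for repeated measures of the score, including an interaction. Its terms are stated as follows: "with between group assignment (training, control) and time (before and after OT) as independent variables". The same model is planned for the mood inventory, HADS and SF-36. Baseline characteristics are to be compared between arms only descriptively.

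The same section limits the data to two visits, gives this as the reason for a per-protocol primary analysis, and leaves only complete pairs: "Missing, unused or spurious primary efficacy data will lead to exclusion of the respective study participant for statistical analysis".

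Table 3 (Study setup/workflow) gives the primary outcome as "Difference in change of total olfactory score between baseline visit and final visit (84+14 days) between both cohorts". On allocation, Randomisation and unblinding specifies a 1:1 ratio and adds: "The assignment will not be based on any stratification factors, and no blocking will be applied".

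**The concern.** Randomisation follows the baseline visit, so the two arms have the same expected baseline score. A group-by-time model with a free baseline mean in each arm does not use that fact. It also fixes at 1 the slope of the day-84 score on the baseline score, instead of estimating it.

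Two things are at stake. One is precision, in a trial expecting about 85 evaluable participants. The other is the estimate in the one trial actually run: without stratification, baseline scores may differ by chance, and a slope fixed at 1 carries regression to the mean into the result. The protocol states this model itself, so the point does not depend on what an unseen analysis plan may add.

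**Working it through.** **Inputs from the protocol.** Two assessments, complete pairs, 1:1 simple randomisation, entry only with an identification score of 12 or lower, two-sided 5% level, N = 100, 15% drop-out (so 100 × 0.85 = 85 evaluable, 42.5 per arm), and responder rates of 28% and 6%.

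**Assumed, because the documents do not give them.** The baseline SD s0, the day-84 SD s1, their correlation ρ, and power of 80%.

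**1. The plan's own figure.** Two proportions, unpooled variance: (1.96 + 0.842)² × (0.28 × 0.72 + 0.06 × 0.94) / 0.22² = 41.8, so 42 per arm and 84 in total. 84 / 0.85 = 98.8, close to the stated 100. N therefore rests on a responder comparison and says nothing about the power of the planned mixed model.

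**2. What the model tests.** With two visits and complete pairs, the interaction is the difference in mean change. On one simulated data set of 85, both routes gave 0.4345 with SE 0.1914.

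**3. Precision.** Up to a common factor, the variances are:
- change score: s0² + s1² − 2ρ·s0·s1
- baseline-adjusted: s1²(1 − ρ²)

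The first minus the second is (s0 − ρ·s1)². This is never negative, and it is zero only when s0 = ρ·s1. With s0 = s1 the ratio of adjusted to change-score variance is (1 + ρ)/2.

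| ρ (equal SDs) | Variance ratio | CI narrower by | Adjusted power where change score has 80% | Patients matching 85 |
|---|---|---|---|---|
| 0.5 | 0.75 | 13% | 89.9% | 64 |
| 0.6 | 0.80 | 11% | 87.9% | 68 |
| 0.7 | 0.85 | 8% | 86.0% | 72 |
| 0.8 | 0.90 | 5% | 84.0% | 77 |
| 0.9 | 0.95 | 3% | 82.0% | 81 |

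**4. Effect of the entry cut-off.** The identification limit truncates part of the baseline score, so s0 may be smaller than s1. If s0 = 0.8·s1, the formulas give ratios of 0.893, 0.941, 0.981 and 1.000 for ρ = 0.5, 0.6, 0.7 and 0.8. Illustrative simulations with a truncated baseline (4,000 trials per setting, 85 patients, simple randomisation; ρ here is the correlation before truncation) gave:
- ρ = 0.5: ratio 0.87–0.88, power 84.1% to 89.0%
- ρ = 0.7: ratio 0.92–0.95, power 82.3% to 84.7%
- ρ = 0.8: ratio 0.95–0.97, power 80.3% to 81.7%

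Since √0.87 = 0.933 and √0.97 = 0.985, the interval is about 1.5–7% narrower.

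**5. Chance baseline difference.** Let the training arm start D higher. The expected day-84 difference is effect + βD. Subtracting the whole of D leaves effect + (β − 1)D. In the simulations the change-score estimate moved by about −0.5, −0.3 and −0.2 per unit of D for ρ = 0.5, 0.7 and 0.8; the adjusted estimate moved by about 0. One SE of baseline imbalance is √(2/42.5) = 0.217 SD. With equal SDs and ρ = 0.7 the shift is −0.3 × 0.217 = −0.065 SD. The SE of the change-score estimate is √(2 × 0.3 × 2/42.5) = 0.168 SD, so the shift is about 0.4 of an SE.

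**6. Validity.** With no true effect, the simulated rejection rate was 4.4–5.4% for the change-score test and 4.6–5.3% for the adjusted test. Both estimates were unbiased over repeated randomisations.

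**The case against.** The strongest defence is that the planned interaction estimates exactly the primary outcome in Table 3, keeps its type I error and is unbiased. The choice is then between two accepted analyses. This stands: nothing here makes the planned result wrong. It is also fair that the equal-SD figures flatter the change, because entry truncates the baseline, and that with a truncated baseline the gain may be small.

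Four stronger readings are tempting, and the documents do not support them.
- A reader might infer that chance imbalance goes uncorrected. It does not: a change score subtracts the whole baseline difference, and what remains is an over-correction in the opposite direction.
- A reader might tie the point to the absence of blocking. Blocking mainly controls arm sizes. Under simple randomisation of 100, an arm difference of 10 or more has probability 37%, but a 45/55 split costs only 1% of efficiency, and baseline adjustment does not alter that.
- A reader might take the time levels, before and after training, to mean day 84 against day 168 for controls. The endpoint definition, Figure 1, the power section and Table 3 all fix baseline to day 84, so this is loose wording only.
- A reader might expect a mixed model with a common baseline mean to retain participants seen only once. The plan's exclusion rule removes them whichever model is used.

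**Conclusion.** The point holds as an efficiency weakness with a conditional shift, not as an error of validity. The stated primary model is a change-score comparison. In large samples adjustment for baseline is at least as precise, and it removes the (β−1)D shift.

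The size cannot be fixed from the documents. Under the assumptions above, adjusted variance is 0.75–0.95 of the change-score variance with equal SDs (ρ 0.5–0.9). It is about 0.87–0.97 with the truncated baseline simulated (ρ 0.5–0.8), which is closer to this trial's entry rule. It is 1 if s0 = ρ·s1.

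All of this treats the analysed patients as randomised groups. What per-protocol exclusions do to comparability is a separate matter that neither analysis settles.

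**What to change.** By dated amendment, before outcomes are analysed by arm, make the primary analysis an ANCOVA of the day-84 total score on arm and baseline total score. The mixed model with baseline means constrained equal across arms is an alternative. Report the adjusted between-arm difference with its 95% CI. Use the same form for HADS, mood inventory, SF-36 and VAS, each with its own baseline. As a wording correction, name the time levels baseline and day 84 in both arms.

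If analysis by arm has already begun, keep the stated model as primary and report the adjusted result as a labelled sensitivity analysis.

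The estimand is unchanged and no new data are needed. The cost is a protocol amendment, which the Ethics and dissemination section says the ethics commission must approve. Retaining participants with one visit would need a separate change to the exclusion rule and is not part of this proposal.

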#### Olfaction, mood and quality of life

An association between olfactory function and depression has been previously established. Signals from the OB flow directly to cortical regions and the limbic system, the latter connection making it an important feature in mood, memory and learning.^23^ Previous research found that individuals with depressive disorders have lower olfactory scores.^8^ Even more, individuals with primary OD had worse scores on the Beck’s Depression Inventory, which correlated with the gravity of dysfunction (categorised as normosmic, hyposmic or anosmic).^8^ Another study found an improvement in total olfactory score to be associated with a decrease in depression severity.^24^ An exploratory randomised controlled clinical trial regarding OT in individuals with major depressive disorder and OD showed no effect; however, the authors suggested that this was due to low compliance.^25^ Besides symptoms of depression, impaired perception of smell was also found to be associated with a smaller social network, higher psychological stress and a lower quality of life (QoL).^26^,^28^ Surprisingly, individuals who performed OT were found to have a higher threshold for pain after training.^29^

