## Methods/design

### Subjects

In this ongoing trial, individuals with persisting COVID-19-associated OD will be included. All participants must be at least 18 years old. Pregnant women or individuals with a history of chronic OD will not be eligible. Female individuals who become pregnant during the study will be allowed to continue, but the data are planned to be excluded from final data analysis as pregnancy could impact olfaction. Persisting OD is defined as hyposmia or anosmia with a duration of at least 12 weeks after confirmed SARS-CoV-2 infection and established as a score of 12 or lower on the identification subscale of the Sniffin’ Sticks testing battery. Prior SARS-CoV-2 infection will preferably be verified by a positive PCR result but can also be established by positive serum levels of antibodies towards SARS-CoV-2 nucleocapsid antigens. All participants are scheduled to undergo routine ENT examination, including anterior rhinoscopy, to exclude non-COVID-19-related pathologies causing OD. There will be no prohibited medication during the trial. A full list of inclusion and exclusion criteria can be found in table 1.

**Table 1 T1:** Overview of inclusion and exclusion criteria

Inclusion criteria	Exclusion criteria
Subject is 18 years or older Confirmed COVID-19 infection by either: PCR results from date of infection Serum antibodies against SARS-CoV-2 nucleocapsid antigens Postinfectious COVID-19-associated OD <13/16 items correct on identification part of the Sniffin’ Sticks Participant is willing to undergo olfactory training over 12 weeks Written ICF is obtained	History of OD prior to COVID-19 infection Nasal pathologies not related to COVID-19 Pregnancy

ICF, informed consent form; OD, olfactory dysfunction.

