### Trial design and safety measurements

The SMELL study is a monocentric trial assessing OT in individuals with persisting COVID-19-associated OD. This study is designed to encompass a screening/baseline visit, followed by a final visit after 12 weeks (day 84+14 days). Written informed consent will be obtained at baseline by a member of the study team (see online supplemental material, available in German). Demographic data and comorbidities are planned to be gathered at the baseline visit through a structured interview. Multiple questionnaires and scales will be completed at this visit. Randomisation is planned after establishing the diagnosis of OD, with one group starting OT immediately after the baseline visit.

OT is set to be performed by the patients after thorough instruction using the Sniffin’ Sticks Duft Quartett, a training kit containing four pens with a distinct scent (clover, eucalyptus, rose and lemon), for 15 min two times per day over a period of 12 weeks. No check-ups between visits will be organised. The same questionnaires and assessments are intended to be conducted at the final visit (day 84+14 days). While this will mark the end of the study for the training cohort, the second cohort will be offered to participate in an open extension phase, performing OT. They will have a third/follow-up visit after another 12 weeks (day 168+14 days). Treatment adherence is planned to be checked using a diary, which will be handed out at baseline, where participants have to check the boxes each day to confirm training. A good compliance is defined as training performance >80% over 12 weeks.

Each adverse event (AE) is expected to be noted in the case report form (CRF), while severe AEs will be reported to the sponsor of the study. Should a subject request or decide to withdraw from the study, all efforts are expected to be made to complete and report the observations as thoroughly as possible up to the end of withdrawal. A safety follow-up will be scheduled for participants who received OT. The primary reason is intended to be stated in the CRF. The sponsor will be authorised to discontinue the study due to relevant medical or administrative causes (eg, insufficient recruitment of participants, non-resolvable problems of data quality and occurrence of unacceptable risks and toxicities). A comprehensive overview of the study flow, completed tests and questionnaires can be found in figure 1 and table 2.

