### Study setup/workflow

Permission for trial performance was given by the ethics committee of the MUI (reference number: 1273/2020). An amendment to include positive serology for antibodies towards nucleocapsid-antigens to establish previous COVID-19 infection was later approved by the ethics committee of the MUI (table 3). Patient recruitment was initiated in August 2022 and is completed. Results of the study are expected later in 2025. The study is registered on ClinicalTrials.gov (NCT05421221).

**Table 3 T3:** Summary of the trial, conform the WHO trial registration data set (V.1.3.1)

Data category	Information
Primary registry and trial identifying number	Federal Office for Safety in Health Care Austria (Bundesamt für Sicherheit im Gesundheitswesen, BASG), 12 732 020
Date of registration in primary registry	16 May 2022
Secondary identifying numbers and registry	ClinicalTrials.gov: NCT05421221 (registration: 13 June 2022)
Source of monetary or material support	Austrian Science Fund (FWF)
Primary sponsor	Medical University of InnsbruckAnichstraße 356020 InnsbruckAustriaE-Mail: [contact]
Secondary sponsor	None
Contact for public and scientific queries(PI and author of the study protocol)	[name] ([contact])Medical University of InnsbruckBH, MD PhD ([contact])Medical University of Innsbruck
Public title	Olfactory Training in COVID-19-Associated Loss of Smell
Scientific title	A randomised controlled trial of the effectiveness of olfactory training on loss of smell related to COVID-19 (SMELL)
Country of recruitment	Austria
Health condition studied	Persisting COVID-19-associated loss of smell
Interventions	Active comparator: olfactory training using the Sniffin’ Sticks Duft Quartett. Duration of 12 weeks (2×/ day)Passive comparator: no changes in daily routine.
Key inclusion and exclusion criteria	Inclusion criteria: prior history of COVID-19 infection (>3 months before study participation) and olfactory dysfunction (score<13/16 on the identification subscale of the Sniffin’ Sticks)Exclusion criteria: history of olfactory dysfunction, nasal pathologies not related to COVID-19, pregnancyA full overview can be found in table 1
Study type	InterventionalAllocation: randomisedSingle-blinded study (investigator)Intervention model: parallel assignmentPrimary purpose: treatmentPhase II
Date of first enrolment	August 2022
Target sample size	Total of 100 participants (1:1 randomisation)
Recruitment status	Completed

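### The primary analysis is per-protocol and compliance is defined only for training, so selected trainees are compared with essentially all completing controls, a comparison that could be biased, probably towards training

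*Protocol article*

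**What the plan says.** All references are to the Protocol article.

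- **Analysis population** (Statistical rationale and outcomes): "the primary analysis is intended to be a per-protocol analysis". Unusable primary efficacy data "will lead to exclusion of the respective study participant for statistical analysis (eg, drop-out or non-compliance to treatment". The reason given is that efficacy is assessed at only two time points, so nothing is interpolated after drop-out. The article mentions no analysis of all randomised participants.
- **Compliance** (Trial design and safety measurements): "A good compliance is defined as training performance >80% over 12 weeks". It is measured with a diary in which "participants have to check the boxes each day to confirm training".
- **Control condition**: allocation is in a "1:1 ratio (training cohort vs natural history" (Randomisation and unblinding). Table 3 (Study setup/workflow) gives "Passive comparator: no changes in daily routine".
- **Primary model** (Statistical rationale and outcomes): a repeated-measures mixed model with group, time and their interaction, tested at the two-sided 5% level.

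**The concern.** The trial asks whether training improves smell more than no training, and the scientific title in Table 3 speaks of effectiveness. That question rests on comparing the groups as randomised. Here one arm is filtered after randomisation by a behaviour for which the other arm has no stated counterpart.

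The setting makes selection plausible. Training takes 15 minutes twice a day for 12 weeks, no contact is planned between visits, and participants know their arm. A trainee who notices no improvement has a reason to stop. If such people are removed from the training arm while their counterparts stay among the controls, the sole primary comparison can show a difference that training did not cause.

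**Working it through.** **1. The plan's own figure.** Inputs from Sample size and power calculation: 28% versus 6% responders, 15% drop-out, N = 100. Power is not stated, so 80% is assumed. With the unpooled normal approximation, two-sided 5%:

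n per arm = (1.960 + 0.842)² × (0.28×0.72 + 0.06×0.94) / 0.22² = 7.85 × 0.258 / 0.0484 = 41.8, rounded up to 42.

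42 / 0.85 = 49.4, rounded up to 50 per arm, total 100. The figure reproduces. It allows for drop-out only; a non-adherent trainee who attends day 84 is not a drop-out.

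**2. Who can be excluded in the first 12 weeks.**

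| Reason | Training arm | Control arm |
|---|---|---|
| No day-84 score | yes | yes |
| Non-compliant, day-84 score present | yes, by training diary | no rule or measure stated |

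The stated reason (two time points, no interpolation) bears on the first row. In the second row both scores exist and there is nothing to interpolate.

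**3. Bias under no true effect.** Let q be the share who would not comply and d how much less they change than others, for reasons unrelated to training. Randomisation puts the same share in both arms. With mean change m among compliers:

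- retained trainees: m
- all controls: m − q·d
- difference: q·d

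**4. Type I error by simulation.** Two-sample t-test on change scores, 43 per arm before exclusion (50 × 0.85 = 42.5), SD 4, 6,000 replicates per cell, non-compliers removed from the training arm only. The SD, q and d are assumptions; none is in the article. Simulation error near 5% is √(0.05×0.95/6000) = 0.3 percentage points. Each cell shows q·d in points, then the two-sided rejection rate.

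| q | d = −2 | d = 0 | d = 2 | d = 4 |
|---|---|---|---|---|
| 10% | −0.2; 4.8% | 0; 4.8% | +0.2; 5.6% | +0.4; 6.8% |
| 20% | −0.4; 7.1% | 0; 5.2% | +0.4; 6.9% | +0.8; 12.4% |
| 30% | −0.6; 8.7% | 0; 4.7% | +0.6; 9.3% | +1.2; 21.5% |
| 40% | −0.8; 11.5% | 0; 4.9% | +0.8; 12.0% | +1.6; 30.0% |

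With non-compliers kept in both arms, mean bias was about 0 and the rejection rate 4.4% to 5.4% in every cell.

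**5. Power, as a side effect.** From 42 per arm, removing 10%, 20%, 30% or 40% of trainees leaves 38, 34, 29 or 25. Holding 28% versus 6% fixed, unpooled power falls from 80% to 77%, 73%, 68% or 62%.

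**The case against.** The strongest reply is that the direction is not established. The article does not say who stops training. People who recover early may stop, which reverses the sign, and if adherence is unrelated to change there is no bias under the null. That stands. A reader might infer that the result is certainly tilted towards training; the documents support only a probable tilt.

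Other stronger readings also fail:

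- **Non-compliers can exist only in the training arm.** Controls are to keep their routine unchanged, so one who took up training could be called non-compliant. What can be said is that the article defines and measures compliance for training alone.
- **The 80% figure is the exclusion cut-off.** It defines good compliance and is not expressly tied to the per-protocol population.
- **Pregnancy exclusions add to the tilt.** Under Subjects, "the data are planned to be excluded from final data analysis as pregnancy could impact olfaction", but this applies to both arms and has no evident one-sided effect.
- **Spurious data will be removed with an eye to the outcome.** The article does not say who decides or how, and a condensed article may leave that to the full protocol.
- **The cited depression trial shows that non-compliers do worse.** Of its null result, "the authors suggested that this was due to low compliance". That is a view about the amount of training, in another population.

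The two-time-point reasoning has some force for participants with only a baseline score, since such a record says little about change. It has none for non-adherent trainees with both scores. The exclusion sentence could also be read as covering non-compliance only where it leaves data unusable, but declaring the primary analysis per-protocol makes that reading hard to sustain.

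A supportive all-randomised analysis in a document not shown would not alter which analysis is declared primary.

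**Conclusion.** The point holds. The article fixes a per-protocol population for the primary analysis of what is in effect a superiority trial, with a post-randomisation exclusion that it defines for one arm only. This breaks the randomised comparison and could bias the result, probably in favour of training.

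The size is illustrative. It runs from −0.8 to +1.6 points over the assumed range and is zero where non-compliers change as others do; the upper type I error of 30% needs 40% excluded and a 4-point difference. These biases are in mean change and should not be read against the article's criterion of more than 4 points, which its sample-size basis uses to classify individuals as improved. Because neither direction nor size can be learned from the participants who are kept, the weakness cannot be argued away after the fact. The point concerns validity; N = 100 is not shown to be wrong.

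**What to change.** Before the analysis is run, define the primary analysis as all randomised participants in their assigned arm, whatever their adherence, using all observed baseline and day-84 scores in the mixed model already planned. Add a sensitivity analysis for missing day-84 scores. Keep the compliance-based analysis as a labelled supportive per-protocol analysis, and state the threshold that defines it.

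The article reports recruitment complete and results expected later in 2025, so the analysis may already have been run. In that case, add the all-randomised analysis, report it as the main result and disclose the change.

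The cost is a wording change and one further model run, with no new data and no change in N. The estimate may be somewhat smaller because non-adherent trainees are included.
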